Pharmacogenomics Study of CPT-11 as the First-line Chemotherapy for Metastatic Colorectal Cancer

1. **Background**

Colorectal cancer (CRC) is the third leading cause of cancer-related deaths in China and leads to nearly 180,000 deaths per year. Irinotecan (CPT-11) combined with 5-FU/LV (FOLFIRI) is recommended as one of the first-line chemotherapy regimens for Metastatic Colorectal Cancer (mCRC).The variation seen in patient response and tolerability remains a clinical challenge. Some clinical studies showed a significant relationship between the gene polymorphisms in key enzymes (eg.UGT1A1, ABCB1, SLCO1B1 etc) involved in the metabolism of CPT-11 and its toxicity. But there are three limitations. Firstly, most of the studies were either retrospective analysis or with small sample size and some of the results were conflict. Secondly, Chinese were rarely included. Thirdly, most of them only used candidate gene approach. By using prospective method, in our study, a larger sample will be enrolled and our aim is to find reliable genetic markers for predicting clinical outcome and toxicity in mCRC patients treated with CPT-11 chemotherapy.

When diagnosed with colorectal cancer, 35% of those patients are stage Ⅳ. Approximately 50%-60% of patients diagnosed with colorectal cancer will develop metastases. Irinotecan is a camptothecin analogue with strong antitumor activity through inhibition of topoisomerase I. Objective response rate (ORR) is about 35%-50%.Compared with treatment with 5-FU/LV, treatment with irinotecan, fluorouracil, and leucovorin resulted in significantly longer progression free survival, higher rate of confirmed response, and longer overall survival. Toxicities associated with irinotecan include both early and late forms of diarrhea (Grade3 to 4 are 22%-30%), and neutropenia (Grade3 or 4 are about 50%). The V308 study had demonstrated that FOLFIRI followed by FOLFOX6 led to longer median Progression-free survival (PFS) and better tolerability in second-line therapy than the reverse sequence.[6](#_ENREF_6) Due to being afraid of the toxicity (e.g. fatal diarrhea) of CPT-11，most doctors in China would like to choose FOLFOX instead of FOLFIRI.

Patients respond differently to identical medications. How to match the right drug to the right person? Nowadays, personalized therapy based on the genotype represents the future direction in cancer treatment.

**
[figure not shown]
**

Fig. 1: **The metabolism of CPT-11** .[7](#_ENREF_7)

CPT-11 is converted to its pharmacologically active metabolite, SN-38 by carboxylesterase1 (CES1) or carboxylesterase2 (CES2) which are both expressed in gastrointestinal tissue, more specifically, within the enterocytes, as well as in the liver. It has been shown that CES2 has a 12.5- to 26-fold higher affinity for CPT-11 than that of CES1.

Three elimination pathways exist for SN-38. First, it can be further conjugated and detoxified by the UDP-glucurono-syltransferase (UGT) enzyme to the ß-glucuronic acid conjugate (SN-38G). Secondly, SN-38 can be eliminated by membrane-localized, energy-dependent outward drug pumps, which facilitate cellular efflux mechanisms. Some of these pumps include proteins belonging to the super family of ABC transporters. One other important transporter involved is the hepatic organic anion transporter (SLCO1B1). These protein transporters are responsible for the biliary and intestinal excretion of CPT-11, and to a lesser degree, of SN-38, and SN-38G. Thirdly, CPT-11 may be eliminated before hydrolysis to its active form by the CYP3A4 enzyme, a member of the cytochrome P450 super family.

CPT-11 functions as an inhibitor of topoisomerase I (Topo1), an enzyme involved in the unraveling of the DNA helix during replication.

Pharmacogenetics, a subset of pharmacogenomics, is a study of genetically determined alterations in metabolic pathways of drug. We have already known some pharmacogenetics information about CPT-11 and most of them originated from small sample study by candidate gene approach. Some of candidate genes are not included in previous studies.

For example, studies has shown that the combination of at least one SLCO1B1 521 T allele, one ABCB1 1236 C allele and one UGT1A1*28 variant 7 repeat demonstrated a statistically significant association with grade 3/4 toxicities in mCRC patients.[7](#_ENREF_7) UGT1A1genotype are strongly associated with severe neutropenia and diarrhea. But the genotype was not related to tumor response or to overall survival (OS). [10](#_ENREF_10) However, Carlini LE’s research showed that UGT1A7 and/or UGT1A9 genotypes may be predictors of response and toxicity in CRC patients treated with capecitabine plus irinotecan.[11](#_ENREF_11) ABCB1 and ABCG2C polymorphism demonstrates different CPT-11 drug exposure.[12](#_ENREF_12) Cytochrome P450 (CYP) polymorphism (e.g.CYP2D6, CYP2C19), was a major source of the heterogeneity in drug exposure. Still there are even more we don’t know yet.

What’s more, in different populations, genotype variants are more or less frequent. Remarkable interethnic differences in the distributions of UGT1A1 genetic polymorphisms have been known. The allele frequency of UGT1A1*28 among Caucasians is higher (0.3 to 0.4) than that among Asians (0.1 to 0.2). On the contrary, other variant alleles in the coding regions were found only in Asians.[13](#_ENREF_13)

Does Topo1 immunohistochemistry have any effect on the clinical response or prognosis for colorectal cancer patients treated with 5-FU/CPT-11 regimen? It is debated now. Some studies showed that it does not differ in TS or Topo-1 expression level in tumor.[14](#_ENREF_14) But some indicated that patients with moderate/high level of Topo-1 benefited from CPT-11.[15](#_ENREF_15) How about Topo1 gene polymorphism? Hoskins demenstrated that TOP1 and TDP1 htSNPs were related to grade 3/4 neutropenia (P = 0.04) and response (P = 0.04), respectively. [16](#_ENREF_16)But that’s not enough.

For the three limitations mentioned in the preface part, we think it is essential to carry out a prospective study in the relationship between the irinogenetics and CPT-11 toxicity, as well as the effectiveness or clinical outcome in China.

1. **Candidate genes**

- Topo1
- Carboxylesterase (CES)
- CYP3A4 cytochrome P450, family 3, subfamily A, polypeptide 4
- UGT1A1
- [ATP-binding cassette (ABC) transporters](http://en.wikipedia.org/wiki/ATP-binding_cassette_transporter)

1. **Objective and endpoints**

**Objective:** To determine the correlation between irinogenetics and irinotecan -related severe toxicities or tumor response in Chinese mCRC patients.

**Primary endpoints:** The correlation between SNP and ORR. The correlation between SNP and adverse events of Grade ≥3 (blood toxicities, diarrhea and any other serious adverse event).

**Secondary endpoints:** The correlation between SNP and PFS/OS.

1. **Research design**

Patients who meet the inclusion criteria 1-12

Record the clinical message

Collect blood samples after the consent of patients

Evaluation of target lesions

AE/toxicity

eg: diarrhe

neutropenia ect.

OS

PFS

Blood samples of each patient

Genoe-wide association study or relavant candidate gene study

The associations of each polymorphism with tumor response, toxicity, and clinical outcome (survival) will be analyzed.

1. **Method**

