**Genome-wide association study**

The GWAS will be conducted using an Affymetrix Genome-Wide Human SNP Array 6.0, followed by a systematic quality control step before the association analysis.

1. **Inclusion and Exclusion criteria**

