12.1 Sample size calculation

**Candidate gene study**

we choose type I error α = 0.05, 1-β = 0.8, two-sided test, provided the target SNP allele frequency in the population was about 20%, treatment efficacy was about 30%, OR ≥ 3.5, the calculated samples size was ≤ 86.

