**GWAS study**

We set statistical limits for the type I error α = 0.01, 1-β = 0.8, two-sided test, provided the target SNP frequency in the population > 15%, and OR> 4, according to the known lowest FOLFIRI first-line treatment induced severe adverse reactions (about 20%) and treatment efficacy (about 30%), we calculate that the needed samples will be 112 by software Quanto (Version 1.2.4), 1:1 ratio.

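### The genome-wide and candidate-gene routes share one set of samples but have separate sizes (112 and ≤ 86), with no single accrual target and no stated order

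*Protocol*

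**What the plan says.** The scheme under Research design in the Protocol takes "Blood samples of each patient" to a "Genoe-wide association study or relavant candidate gene study". There is one set of samples, two possible routes, and no rule for choosing between them.

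The Method section describes both routes. Under Genome-wide association study it is unconditional: "The GWAS will be conducted using an Affymetrix Genome-Wide Human SNP Array 6.0".

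Section 12.1 gives each route its own calculation:

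- **Candidate gene study:** alpha 0.05 two-sided, power 0.8, allele frequency near 20%, response near 30%, OR of at least 3.5. The result is a bound: "the calculated samples size was ≤ 86".
- **GWAS study:** alpha 0.01 two-sided, power 0.8, SNP frequency above 15%, OR above 4, severe adverse reactions about 20%, response about 30%, 1:1 ratio. Here "we calculate that the needed samples will be 112".

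Section 12.2 then uses a two-sided 0.05 level throughout, without distinguishing the routes.

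**The concern.** The Research design and the Method section disagree on whether the GWAS is an alternative or a certainty. The two sizes in section 12.1 are not tied to one enrolment figure. A site team reading the protocol cannot tell when accrual is complete, and an analyst cannot tell which analysis carries the primary objective.

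The sizes are not interchangeable. The larger covers the candidate inputs, but the smaller does not cover the GWAS inputs. A study that enrols 86 and runs the array follows the text and falls short of its own power statement. Because no order or role is given, the protocol also leaves open whether a small set of mechanism-based SNPs or a whole array is the confirmatory test.

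**Working it through.** **Inputs.** All come from section 12.1, taken at their stated bounds.

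- Candidate: allele frequency q = 0.20, OR = 3.5, response rate 0.30, alpha 0.05 two-sided.
- GWAS: q = 0.15 (read as an allele frequency), OR = 4, outcome rate 0.20 or 0.30, alpha 0.01 two-sided.
- Assumed: Hardy-Weinberg genotypes and a dominant (carrier) model, because the protocol names no genetic model. No allowance is made for dropout or failed genotyping, since none is stated.

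**Method.** Likelihood-ratio calculation for a carrier-by-outcome table.

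- Carrier frequency P = 1 − (1 − q)². The risks in non-carriers and carriers are solved so that they average to the outcome rate and have the stated OR. They give the carrier proportion in cases, a, and in controls, b.
- With case fraction c and m = c·a + (1 − c)·b, the expected statistic per subject is λ = 2[c·D(a,m) + (1 − c)·D(b,m)], where D(x,m) = x·ln(x/m) + (1 − x)·ln((1 − x)/(1 − m)).
- Required N = (z₁₋α/₂ + 0.842)² / λ for 80% power. Power at N = Φ(√(Nλ) − z₁₋α/₂).

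**Step 1: reproduce the protocol's sizes (1:1, c = 0.5).**

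- Candidate: P = 0.36, a = 0.566, b = 0.272, λ = 0.09065. N = (1.960 + 0.842)² / 0.09065 = 86.6, in line with 86.
- GWAS, 20% outcome: P = 0.2775, a = 0.524, b = 0.216, λ = 0.10427. N = (2.576 + 0.842)² / 0.10427 = 112.0, matching 112.
- GWAS, 30% outcome: λ = 0.09910, N = 117.8. So 112 is tied to the 20% toxicity rate.

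Both sizes follow from their own inputs. The fault is not arithmetic.

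**Step 2: exchange the sizes, keeping 1:1.**

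- GWAS inputs at 86, 20% outcome: √(86 × 0.10427) = 2.994; Φ(2.994 − 2.576) = 66%. With the 30% outcome: 63%.
- Candidate inputs at 112: √(112 × 0.09065) = 3.186; Φ(3.186 − 1.960) = 89%.

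**Step 3: the cohort the protocol describes.** Patients are enrolled on eligibility, not on outcome, so the case fraction c is the outcome rate itself.

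| Inputs | λ | N for 80% | Power at 86 | Power at 112 |
|---|---|---|---|---|
| Candidate, 30% response | 0.07740 | 102 | 73% | 84% |
| GWAS, 20% events | 0.06977 | 168 | 45% | 59% |
| GWAS, 30% response | 0.08613 | 136 | 56% | 70% |

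**Sensitivity to the model.** Under a log-additive model the unselected-cohort GWAS power is 59% (20% events) or 67% (30%) at 86, and 73% or 81% at 112. That model does not reproduce the stated sizes: at 1:1 it gives 90% rather than 80% at both 86 (candidate) and 112 (GWAS, 20%). The dominant model reproduces both, so it is the better guide to what was calculated.

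All these powers are per SNP at the stated alpha, before any correction for the number of SNPs.

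**The case against.** The best defence is that the either/or is an artefact of a terse flow diagram. The Method section describes both routes, section 12.1 sizes both, and the Background criticises earlier work for relying on candidate genes alone. A sensible reader would conclude that both analyses run in one cohort and that 112, being larger, covers both. That is a reasonable inference, and the fix adopts it. But the protocol does not say it, and 112 does not cover both: in an unselected cohort it falls short of 80% for the GWAS inputs under the model that reproduces the stated sizes.

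A second objection is that testing order and confirmatory status are commonly left to the statistical analysis plan, which is not shown. This has some force for the details. It does not excuse the accrual target, or two sections of the protocol that disagree on whether the GWAS is optional.

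Two stronger readings should be resisted.

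- A reader might infer that the sponsor means to pick the route once results are known. The text fixes no time for the choice, so it does not rule this out, but it states nothing of the kind.
- A reader might also want to put a figure on the error inflation from having two routes. That requires each route to hold a stated family-wise error rate. Section 12.2 gives only a 0.05 level with no family-wise control, so the documents offer no basis for such a figure.

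**Conclusion.** The point holds as an unresolved design choice with a measurable effect on power. Stopping at 86 and running the array is consistent with the text but gives about 66% power on the protocol's own 1:1 assumption, and about 45% (20% events) or 56% (30%) in the cohort it describes, against the stated 80%.

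These figures rest on the dominant model, Hardy-Weinberg proportions, and frequency and OR taken at their bounds. The candidate size is itself a bound, so 86 is the most that route claims to need. The 66% should not be written into the protocol as a replacement: like the 80%, it assumes equal cases and controls, which eligibility-based enrolment will not produce.

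**What to change.** 1. Reconcile the Research design with the Method section by stating that both routes run in one cohort.
2. State one accrual target, the protocol's own 112.
3. The protocol lists candidate genes, not SNPs. Apply its selection rule under Relevant candidate gene study (functional SNPs, minor allele frequency above 0.15, the stated locations) to produce a fixed SNP list before genotypes are linked to outcomes. Test that list first, as the only confirmatory family.
4. Label the array analysis exploratory.
5. Withdraw the GWAS 80% power claim, or restate it for an unselected cohort of 112: about 59% at 20% events and 70% at 30% response, with the genetic model named.
6. State the candidate power at 112 as about 84% per SNP at alpha 0.05 and 30% response, before any multiplicity correction. Correction across the SNP list will lower it.

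This is a change of wording and needs no more patients than the larger figure already in the protocol. The downside is that array findings lose confirmatory status. If the sponsor wants 80% power for the GWAS inputs in this cohort even at alpha 0.01, the same calculation asks for 168 patients (20% events) or 136 (30%).

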**Relavant candidate gene study**

Gene Oncology ([http://www.geneontology.org](http://www.geneontology.org/)) and the National Center for Biotechnology Information (NCBI) Gene database (<http://www.ncbi.nlm.nih.gov/gene>) and related literature to identify all functional single nucleotide polymorphisms (SNPs) of relavant genes with a minor allele frequency of more than 0.15 and a location in the promoter untranslated region or coding region of the gene.

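### The SNP-only, MAF > 0.15 candidate rule, read literally, leaves out the UGT1A1\*28 repeat, and the candidate gene list omits SLCO1B1, though the Background relies on both

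*Protocol*

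**What the plan says.** - **Selection rule.** The Method section on the candidate gene study admits "functional single nucleotide polymorphisms (SNPs) of relavant genes with a minor allele frequency of more than 0.15", with "a location in the promoter untranslated region or coding region of the gene". The genes are to be found from two databases "and related literature to identify all functional single nucleotide polymorphisms (SNPs) of relavant genes".
- **UGT1A1\*28.** The Background describes it as a repeat, within a three-marker combination: "one SLCO1B1 521 T allele, one ABCB1 1236 C allele and one UGT1A1*28 variant 7 repeat". It ties that combination to grade 3/4 toxicity, and UGT1A1 genotype to severe neutropenia and diarrhoea. On frequency: "The allele frequency of UGT1A1*28 among Caucasians is higher (0.3 to 0.4) than that among Asians (0.1 to 0.2". Of further variants in the same gene it says that "other variant alleles in the coding regions were found only in Asians", without giving a frequency.
- **Gene list.** The Candidate genes section lists Topo1, carboxylesterase, "CYP3A4 cytochrome P450, family 3, subfamily A, polypeptide 4", UGT1A1 and the ABC transporters. SLCO1B1 is not there, although the Background names it among the key genes and again as an important transporter.
- **Endpoints and analysis.** The primary and secondary endpoints are all correlations with SNPs. Section 12.2 plans a multivariable logistic regression to find which genotype predicts response or toxicity independently.
- **Other route.** The Research design offers a genome-wide study or a candidate gene study. The genome-wide study uses a SNP array.

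**The concern.** The protocol justifies itself by conflicting earlier results on irinotecan toxicity markers and by how rarely Chinese patients were studied. One would expect the markers it cites to be among those certain to be typed. As the rule is worded, UGT1A1\*28 is not certain to be typed, and SLCO1B1 depends on how the term for the relevant genes is read.

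The consequence goes beyond one missing test. The regression in section 12.2 can establish independence only from variants that are in the data set. Without \*28, a SNP associated with toxicity because it is inherited together with \*28 could not be told apart from a marker in its own right. Nor could the cited three-marker combination be checked in Chinese patients.

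**Working it through.** **Step 1. UGT1A1\*28 against each part of the rule.**

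| Rule | What the protocol says of \*28 | Result |
|---|---|---|
| Single nucleotide polymorphism | 7-repeat variant | Fails on the literal wording, at any frequency |
| Minor allele frequency above 0.15 | 0.1 to 0.2 in Asians | Fails from 0.10 to 0.15; passes above 0.15 up to 0.20 |
| Gene is relevant | UGT1A1 is on the candidate list | Passes |

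The variant type settles the literal reading. Frequency alone does not, because the stated range straddles the cut-off.

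**Step 2. The other cited markers.**

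- SLCO1B1: absent from the list. No allele frequency is given.
- ABCB1: covered by the ABC transporter entry.
- Asian coding-region variants of UGT1A1: the rule expressly allows a coding location, and no frequency is given. Nothing can be computed.

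**Step 3. How many patients carry \*28.** With allele frequency q and Hardy-Weinberg proportions, the carrier proportion is 1 − (1 − q)².

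| q | Carriers | Of 86 (candidate study) | Of 112 (genome-wide study) | What excludes it |
|---|---|---|---|---|
| 0.10 | 1 − 0.90² = 0.190 | 16 | 21 | SNP wording and frequency |
| 0.15 | 1 − 0.85² = 0.278 | 24 | 31 | SNP wording and frequency |
| 0.20 | 1 − 0.80² = 0.360 | 31 | 40 | SNP wording only |

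**Step 4. What typing it would yield.** Section 12.1 gives two-sided α = 0.05, 80% power, allele frequency about 20%, outcome rate about 30%, OR ≥ 3.5 and a sample of at most 86. It names no genetic model. A 1:1 case-control calculation with dominant coding (expected likelihood-ratio test) gives 44 + 44 = 88, and exactly 86 if the outcome rate is 20%. The stated figure is therefore reproduced closely, with dominant coding as an assumption.

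The patients are in fact one treated cohort, so power is taken for a cohort of 86. Let c be the carrier proportion and K the overall outcome rate. The risks p0 (non-carriers) and p1 (carriers) solve (1 − c)p0 + c·p1 = K with odds ratio 3.5. With H(p) = p ln p + (1 − p) ln(1 − p):

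- information per patient: λ = 2[(1 − c)H(p0) + c·H(p1) − H(K)]
- power: Φ(√(86λ) − 1.96)

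| q | K | p0 | p1 | λ | √(86λ) | Power |
|---|---|---|---|---|---|---|
| 0.10 | 0.30 (response) | 0.246 | 0.532 | 0.0563 | 2.200 | 0.595 |
| 0.10 | 0.20 (toxicity) | 0.155 | 0.391 | 0.0474 | 2.019 | 0.524 |
| 0.20 | 0.30 (response) | 0.203 | 0.472 | 0.0774 | 2.580 | 0.732 |
| 0.20 | 0.20 (toxicity) | 0.125 | 0.333 | 0.0603 | 2.276 | 0.624 |

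The 20% toxicity rate is the one that section 12.1 uses for the genome-wide study. Under the 1:1 design with K = 0.30, power at q = 0.10 is 0.65. For \*28 the toxicity rows matter more, since the Background cites evidence that UGT1A1 genotype was not related to tumour response.

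**The case against.** The strongest reply has four parts.

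1. *A frequency floor is a normal choice that protects power, and it fits the sizing inputs (about 20% and above 15%).* This stands for discovery SNPs. It is weaker for a handful of markers with prior evidence, where an estimate with a wide interval is still worth having.
2. *SNP may be loose wording.* The protocol elsewhere speaks of polymorphisms, and UGT1A1 is on the list, so the investigators may well intend to type \*28. This is plausible. It shows that the rule needs correcting, because the selection rule and the endpoints both use the narrower word.
3. *The gene list is not stated to be closed.* The rule draws on databases and literature and does not refer back to the list, so SLCO1B1 could be counted as relevant. This stands: the omission is an inconsistency, not proof of exclusion. An open list does not bring a repeat into a SNP-only rule.
4. *The genome-wide route has no gene list and no frequency cut-off in its method section.* It could reach SLCO1B1 and coding SNPs. But it is only an alternative, its sample size assumes a frequency above 15%, and the protocol makes no provision for typing a repeat on a SNP array.

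A reader might also infer that the rule shuts out every marker the Background cites, including the Asian coding variants. The protocol does not support that: it gives no frequency for those variants, admits coding SNPs, and covers ABCB1 through the ABC entry.

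**Conclusion.** The concern holds in limited form. Followed literally, the candidate rule leaves out UGT1A1\*28 because of its variant type, and it would also do so on frequency over the lower half of the protocol's own Asian range. The gene list omits SLCO1B1, contrary to the Background. Neither gap is reliably closed by the genome-wide alternative, although that could reach SLCO1B1.

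About 19% to 28% of patients would carry \*28 at q = 0.10 to 0.15, and up to 36% at q = 0.20. That upper figure must not be blamed on the frequency cut-off, which \*28 passes there. If the variant is untyped, independence from it cannot be shown for any other marker.

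It would go too far to say that the trial cannot test these markers. That follows only for \*28, and only on the candidate route with SNP read literally. The carrier figures assume Hardy-Weinberg proportions and the protocol's own frequency range. The power figures further assume dominant coding and a single cohort.

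**What to change.** - Keep MAF > 0.15 for discovery SNPs. Add a short pre-specified list to be typed regardless of frequency and variant type: UGT1A1\*28 and the SLCO1B1 521 and ABCB1 1236 variants of the cited combination.
- Add SLCO1B1 to the Candidate genes section.
- Replace SNP by polymorphism in the primary and secondary endpoints, so that a repeat can count.
- In section 12.2, state that toxicity associations are also shown adjusted for UGT1A1 genotype.

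Cost: a few targeted genotypes on blood already collected, with no extra patients or visits. There will be a few more tests at the unadjusted 0.05 level. Precision will be lower for rarer variants: about 52% to 60% power at an allele frequency of 0.10 with 86 patients and OR 3.5, on the assumptions above. The protocol should say so, so that a null result for a rare variant is not read as evidence of no effect.
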